**Sexual health outcomes**	
Sexual partners	Sexual partners
Condom use—episodes and partners	Condom use—episodes and partners
Self-reported STI diagnoses	Self-reported STI diagnoses
Contraception use and pregnancy	Contraception use and pregnancy
Health-related quality of life	Health-related quality of life
	Service use
**Mediators of condom use**	
Motivation to use condoms	Motivation to use condoms
Intentions to use condoms	Intentions to use condoms
Beliefs about pleasure	Beliefs about pleasure
Non-condom use due to intoxication	Non-condom use due to intoxication
	Evaluation of condom use
	Communication
	Identity
	Self-efficacy
	Condom problems
	Knowledge

#### Outcome measures

The online outcome measurement instrument is detailed in full in online supplementary appendix 2.

##### Demographics

Questions at baseline will collect demographic information including age, employment status and ethnicity.

##### Condom use

The objective of the study is to promote condom use with female partners, so the primary outcome is the number of episodes of unprotected vaginal sex (without a condom) over the previous 3 months, assessed at the 3-month follow-up. We expect the majority of change in behaviour to occur shortly after recruitment, as we expect users will be most likely to engage with the intervention during the clinic visit.

##### Sexual partners

Participants will be asked to report the number and type of sexual partners over the past 3 months (both female and male). We will also assess the number of partners participants have had unprotected sex with over the previous 3 months: female (vaginal and anal sex) and male (anal sex).

##### Contraception use and pregnancy

Participants will be asked to indicate which types of contraception (if any) they are using with current partners. Participants will be asked whether a female partner has been pregnant in the past 3 months, and the outcome of that pregnancy (if known).

##### STI diagnoses

Participants will be asked to report STI diagnoses over the past 3 months at every follow-up point. We will also assess whether participants have received treatment due to a partner being diagnosed with an STI. In order to assess laboratory diagnoses, all STI diagnoses recorded in sexual health clinic records (in the participating sites) over the study period will be noted at 12 months.

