### The intervention

The MenSS website content and design was developed based on evidence from the sexual health research literature and theories of behaviour change, qualitative interviews with men in sexual health clinics, and discussions with clinical and academic experts in sexual health and digital technologies.^19^ The development process was iterative, with a high level of user involvement. The intervention is designed to be delivered initially in clinic, to make use of the time when patients are waiting to be seen, but also providing (and encouraging) online access after patients have left the clinic.

The MenSS intervention consists of an interactive website. While in clinic, users will be presented with a tailored package of website content which addresses individual men's barriers to condom use. The site targets a number of influences on effective condom use, such as:
Condom knowledge (eg, about sizes and types of condoms);Condom use skills;Difficulties in negotiating condom use;Inaccurate beliefs about STI risk;Social influences, such as perceived/expected partner response;Sexual pleasure;Being caught in the ‘heat of the moment’;Alcohol and drug use.

While in clinic, users will be asked to select their own personal barriers to condom use. This task will produce a tailored package of information, offering solutions or counter-arguments to barriers (including interactive activities and quizzes, videos and case vignettes), which will be presented prominently on the homepage. Some content is presented to all users (eg, training in condom use skills), and all content will be available via website navigation tabs. Participants will be led through their tailored content package sequentially, and will be asked to set goals to change their behaviour. If wanted, participants will receive emails to assess achievement of goals, and to encourage them to visit the intervention website again.

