#### Follow-up data collection

At 3, 6 and 12 months after their initial clinic visit, participants will receive an automated email asking them to complete a follow-up questionnaire (see Outcome assessment section), by clicking on a weblink to an online questionnaire. If they do not complete the questionnaire, they will receive three further email prompts, at 1-week intervals, as well as two text messages to their mobile phone (again including the weblink) alongside the latter two emails. If participants still do not respond, the researcher will telephone participants a week after the final email to remind them to fill in the study questionnaire. Information about STI diagnoses will be collected at all time points via self-report, and at 12 months by recording diagnoses or suspected diagnoses over the past year recorded in the clinical notes at the sexual health clinics participants are recruited from.

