### Inclusion and exclusion criteria

#### Inclusion criteria

Men aged 16 years and above (with no upper age limit); able to read English; with access to the internet; and at high risk of future STI (ie, two or more partners in the past year (male or female) and some non-condom use in the past 3 months; or symptoms of acute STI; or seeking treatment for an STI); and for whom at least half of their sexual partners are female.

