### Randomisation

Once participants have been checked for eligibility, given informed consent, and submitted baseline data, they will be allocated by the computer algorithm randomisation system to either the intervention or control group. The participant will be informed with an automated message on the tablet computer, and this allocation will be unalterable.

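### Read literally, the 12-month clinic-record window counts infections first diagnosed at the recruitment visit as follow-up STIs, which pulls relative STI effects towards no effect

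*Protocol article*

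**What the plan says.** All places are in the protocol article.

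- **Who enters.** Under Inclusion criteria, two or more partners with some non-condom use is one route to being at high risk. The others are "or symptoms of acute STI; or seeking treatment for an STI".
- **When.** The section on the intervention says that delivery starts in clinic "to make use of the time when patients are waiting to be seen". Under Randomisation: "Once participants have been checked for eligibility, given informed consent, and submitted baseline data, they will be allocated by the computer algorithm".
- **Time zero.** Follow-up questionnaires are sent "At 3, 6 and 12 months after their initial clinic visit".
- **Notes review.** The STI diagnoses section says that "all STI diagnoses recorded in sexual health clinic records (in the participating sites) over the study period will be noted at 12 months". Follow-up data collection describes the same exercise as done "by recording diagnoses or suspected diagnoses over the past year recorded in the clinical notes".
- **Self-report.** "Participants will be asked to report STI diagnoses over the past 3 months at every follow-up point".
- **Use.** The Outcome assessment section names cumulative STI incidence, from self-report and clinical notes, as an outcome. The Cost-effectiveness analysis section builds STIs prevented (chlamydia or gonorrhoea) from the 12-month records together with self-reported episodes.

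**The concern.** The objectives concern STI acquisition, and the outcome is labelled incidence. A man who arrives with an undiagnosed infection is randomised, then seen, and his infection is recorded after time zero. Neither description of the notes review sets that episode apart. Because one of them also takes suspected diagnoses, the symptoms that made a man eligible could themselves register as an outcome.

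The website cannot prevent an infection that is already there. Such infections add about the same number of cases to each arm, which moves any ratio towards 1 and raises the apparent event rate. The planned analysis would not correct this. Adjustment is for the baseline value of each outcome, and the baseline STI item is a self-report given before the consultation. The clinic-record outcome has no baseline counterpart in Table 1. At stake is what the pilot can say about the website's relative effect on STI.

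**Working it through.** **The plan's own figures.** The protocol states no STI rate, STI effect or STI power, so there is nothing on this point to reproduce. The sample size is for unprotected-sex episodes. Solving SD = 1.35 / [(z for alpha + z for power) × √(2/n)] gives 2.68 for 83 per arm at 90% power and 2.66 for 61 per arm at 80%. The two statements agree with each other and do not depend on STI.

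**Sequence.** Eligibility, consent, baseline data and randomisation take place in one tablet session in the waiting room. The consultation follows, with any diagnosis made then or from tests taken then. The diagnosis is therefore recorded after time zero, within the study period and within a 12-month look-back to that visit.

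**Assumed inputs (none is in the documents).** b = share with an infection first diagnosed at the recruitment visit, equal in expectation in the two arms, 5–20%. p = true 12-month risk of a new STI in controls, 5–15%, independent of b. True risk ratio 0.70.

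**Any STI recorded.** Counted risk = 1 − (1 − b)(1 − p), with 0.70p in place of p in the intervention arm.

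At b = 10%, p = 10%:
- control: 1 − 0.90 × 0.90 = 0.190
- intervention: 1 − 0.90 × 0.93 = 0.163
- observed ratio: 0.163 / 0.190 = 0.86
- risk difference: 0.027 instead of 0.030, that is, multiplied by (1 − b)
- apparent control event rate: 19% instead of 10%

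Observed ratio over the range (true value 0.70):

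| | p = 5% | p = 10% | p = 15% |
|---|---|---|---|
| b = 5% | 0.85 | 0.80 | 0.78 |
| b = 10% | 0.91 | 0.86 | 0.83 |
| b = 20% | 0.95 | 0.91 | 0.89 |

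The extremes are 0.14975 / 0.1925 = 0.78 and 0.228 / 0.240 = 0.95. Among control men counted as having an STI, the share carrying a recruitment-visit infection runs from 0.05 / 0.1925 = 26% to 0.20 / 0.24 = 83%.

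**Episodes, as in cost per STI prevented.** Expected count per man = b + p. At b = 10%, p = 10% this is 0.20 against 0.17. The difference is 0.03, exactly as without the recruitment-visit infections, because b cancels. Two things do change:
- The ratio of counts becomes 0.17 / 0.20 = 0.85.
- If the variance of a count equals its mean, the standard error of the difference rises by √(0.37 / 0.17) = 1.48.

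Chance imbalance in recruitment-visit infections alone, with 83 men per arm, has a standard error of √(2 × 0.10 × 0.90 / 83) = 4.7 percentage points at b = 10%, and √(2 × 0.20 × 0.80 / 83) = 6.2 points at b = 20%. The true difference in this example is 3 points.

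**The case against.** The best reply is that no sentence says outright that recruitment-visit infections count as outcomes. The text says that diagnoses will be noted, the outcome is called incidence, and the article refers to a statistical analysis plan that is not shown and could narrow the window. That stands as a limit on certainty. It does not remove the point, because the article states a collection rule: all diagnoses, and those of the past year. If notes are extracted without dates, no later analysis rule can separate the two kinds of infection.

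Other parts of the reply hold, and they mark where a reader might infer too much:

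- **That STIs prevented is diluted.** The expected difference in episodes is unchanged. Only its precision suffers.
- **That the 3-month questionnaire has the same fault.** Its wording is in a supplementary appendix that is not shown. The 3-month recall touches the visit only at its edge: men who answer after later prompts have a window that starts after the visit, and the 3-month recall at 6 and 12 months does not reach it.
- **That baseline data miss every infection present at entry.** A man seeking treatment may already hold a diagnosis and report it. The gap concerns infections first diagnosed at the visit.
- **That most men enter with an infection.** The protocol gives no split between the entry routes.
- **That the phase III trial will be wrongly sized.** The sample size section says that effect sizes of key outcomes, naming condom use, will inform later power calculations. It does not say that the STI rate will.

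**Conclusion.** The point holds, at moderate severity. Followed literally, the clinic-record window mixes infections present before randomisation with those acquired afterwards, and the planned baseline adjustment cannot separate them. Ratio measures and the proportion with any STI move towards no effect, and the apparent event rate rises. The observed ratio is about 0.86 for a true 0.70 at 10% prevalence and 10% incidence, and 0.78–0.95 over the assumed range. All these sizes rest on assumed rates, on equal expected prevalence in the arms, and on men being seen after randomisation, as the intervention section describes.

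It is tempting to treat this as a fault that undermines the trial or could create a false benefit. The documents do not support that. The trial is a pilot aimed mainly at recruitment, retention, engagement and acceptability; STI is secondary with no stated power; and the economic analysis is an initial one that mainly tests whether the data are fit for purpose. The primary outcome and the sample size of 166 are unaffected. The expected bias in the ratio is towards no effect, although in one trial of this size chance imbalance could push the estimate either way.

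**What to change.** 1. In the notes extraction, record the specimen or visit date of each diagnosis.
2. Count as outcomes only diagnoses from specimens taken after the recruitment episode, excluding that visit and its results within a short window fixed in advance. Word the two descriptions of the notes review to match.
3. Keep diagnoses from the recruitment visit as a separate baseline variable and adjust STI comparisons for it.
4. If the 3-month item does not already do so, ask men not to count tests done at the visit when they joined.

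The cost is one date field, one baseline flag and possibly one phrase in the questionnaire. The downside is small: a few early re-infections inside the window are lost.

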##### Health-related quality of life

Health-related quality of life (HRQoL) will be assessed using the EQ-5D,^23^
^24^ which is a 5-item, 3-level questionnaire covering self-care, usual activity, anxiety and depression, and pain and mobility. We will also use a newly developed sexual health Quality of Life Scale,^25^ and compare its performance with the EQ-5D, to assess its suitability for outcome assessment in a sexual health context.

##### Service use

Use of a variety of sexual health services over the period of the study will be assessed (eg, sexual health clinics, general practice, outreach services).

#### Measuring mediators of condom use

While it is important to assess changes in behaviour, it is also important to assess the mediators of behaviour change. This provides information about the mechanisms by which behaviour might have changed. The mediators measured were identified following consultation with experts, a review of the literature, interviews with the target population, and using the theoretical frameworks of the COM-B model^26^ and the PRIME theory of motivation.^27^

##### Condom use errors and problems

To ensure that condom use is ‘correct’, and to assess any impact on condom use skills, we will assess condom use problems at all time points, using a measure defined by Crosby *et al*,^28^ which assesses the occurrence of 15 condom errors and problems within the past 3 months. The scale was adapted in the light of qualitative fieldwork, to improve relevance and clarity.

##### Knowledge

Knowledge (of risk of STIs and condom sizes) will be assessed using an 11-item measure, devised based on gaps in men's knowledge identified in the literature and in interviews with the target population. A number of ‘true or false’ statements regarding misconceptions about condoms and risk will be given (eg, ‘You would know if you had an STI, without needing a test’; ‘Standard sized condoms are suitable for all men’).

##### Communication with partners

To assess communication with partners over a 3-month period, we adapted the six-item Partner Communication Scale.^29^ The scale was adapted in the light of qualitative fieldwork, and the recall period was modified from 6 to 3 months, as follow-up assessments will be 3 months apart.

##### Identity

To assess potential links between identity (self-perception) and condom use,^27^ we created a seven-item scale, derived from issues relating to condom use identity that had been identified during the fieldwork.

##### Beliefs about pleasure

Beliefs about pleasure will be assessed using an eight-item scale, adapted from the ‘Effect of sexual experience’ subscale of the Condom Perceived Barriers Scale.^30^ The scale was adapted in the light of qualitative fieldwork, to improve relevance and clarity.

##### Self-efficacy

Self-efficacy will be assessed using a 14-item measure, adapted from the widely validated Brafford and Beck Scale.^31^ The scale was adapted in the light of qualitative fieldwork, to improve relevance and clarity.

##### Motivation, intention and evaluation of condom use

Motivation (want) and intention to use condoms, and evaluation of condom use will be assessed using single-item measures ([name], 12 September 2013, personal communication).

##### Alcohol and drug use

Alcohol and drug use were found in our fieldwork to be important factors in non-condom use. We therefore included a single item assessing the number of times in the past 3 months that participants had unprotected sex when intoxicated.

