#### Measures

In the light of evidence that measurement alone may prompt behaviour change,^22^ we will measure a limited number of outcomes (condom use and the main mediators, and self-reported STI diagnoses) at baseline; we will also assess a full range of outcomes at 3, 6 and 12 months (table 1). All assessments have a recall period of the previous 3 months, which is the time between follow-up assessments.

**Table 1 BMJOPEN2014007552TB1:** Variables assessed at each time point

Baseline measures	3-month, 6-month and 12-month follow-up assessments
Demographic details (age, occupation, ethnicity)	

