#### Mediation analyses

We will conduct a prognostic model in order to determine whether change in any of the mediating variables (eg, beliefs about pleasure, self-efficacy) is associated with any intervention effects. This will help to identify which elements of the website seem to be most influential.

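### The intoxication item listed as a mediator counts unprotected sex and so largely overlaps the primary outcome; if the intervention works, the mediation analysis can credit intoxication spuriously

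*Protocol article*

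**What the plan says.** The primary outcome is defined under Condom use: "the primary outcome is the number of episodes of unprotected vaginal sex (without a condom) over the previous 3 months", assessed at the 3-month follow-up. Under Measures, the same window is set for every item: "All assessments have a recall period of the previous 3 months, which is the time between follow-up assessments".

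Table 1 places "Non-condom use due to intoxication" among the mediators of condom use, at baseline and at each follow-up. The section Alcohol and drug use says what is actually asked: "We therefore included a single item assessing the number of times in the past 3 months that participants had unprotected sex when intoxicated". The article describes no separate measure of drinking, of drug use, or of sex while intoxicated regardless of condom use.

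Under Mediation analyses, a prognostic model is to "determine whether change in any of the mediating variables (eg, beliefs about pleasure, self-efficacy) is associated with any intervention effects". No listed mediator is excluded. The stated purpose is: "This will help to identify which elements of the website seem to be most influential". One of the website's content areas, listed under The intervention, is "Alcohol and drug use".

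**The concern.** A mediator has to be something other than the outcome that it is meant to explain. This item is a count of outcome events that happened under a particular condition. When total unprotected episodes fall, the intoxicated ones fall with them, whatever caused the fall. The item and the outcome therefore move together by construction. Having a baseline value for the item, or measuring it at an earlier visit, would not change what it counts.

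The Table 1 label makes this worse. It speaks of non-condom use caused by intoxication, while the item as described counts episodes that coincided with it. A count of coinciding episodes cannot support the causal label.

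At stake is the use made of the result. The mediation analysis is meant to point to the influential parts of the website, and this artefact maps directly onto one named content area. A pilot meant to optimise a phase III trial could draw the wrong lesson about that content.

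**Working it through.** **Inputs from the protocol** (Sample size and power calculations): a reduction of 1.35 episodes; 83 per arm for 90% power; 61 per arm for 80% power; two-sided α of 0.05. The SD and the mean are not given.

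**Step 1: the implied SD.** The two-sample normal formula is n per arm = 2(z_α + z_β)²·SD²/Δ², so SD² = n·Δ²/[2(z_α + z_β)²].
- 83 per arm, 90%: 83 × 1.8225 / (2 × 10.507) = 7.20, SD 2.68.
- 61 per arm, 80%: 61 × 1.8225 / (2 × 7.849) = 7.08, SD 2.66.

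The two statements agree with each other at an SD of about 2.67 (variance about 7.13). This is a back-calculation, not an independent check of the SD.

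**Step 2: the artefact in closed form.** Let N be the number of unprotected episodes, with variance-to-mean ratio phi. Let X be the number of these when intoxicated, with X given N binomial(N, p) and p the same in both arms. Intoxication then plays no part in the intervention effect Δ.
- Arm effect on X: p·Δ.
- Within arm: Cov(X, N) = p·phi·mean and Var(X) = p·mean·[(1−p) + p·phi].
- Slope of N on X: phi/[(1−p) + p·phi].
- Share of the effect apparently explained: p·phi/[(1−p) + p·phi].

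**Step 3: numbers.** At an assumed mean of 6, phi = 7.13/6, about 1.2.

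| Intoxicated share p | Calculation | Spurious share |
|---|---|---|
| 0.1 | 0.12/1.02 | 12% |
| 0.2 | 0.24/1.04 | 23% |
| 0.3 | 0.36/1.06 | 34% |
| 0.5 | 0.60/1.10 | 55% |

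At an assumed mean of 2.5 with the same SD, phi = 7.13/2.5 = 2.85, and the share is 0.57/1.37 = 42% at p = 0.2 and 1.425/1.925 = 74% at p = 0.5.

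**Step 4: simulation at the trial's size.** The set-up was an overdispersed count with control SD about 2.67, control mean 2.5 to 5, a reduction of 1.35, and an intoxicated share unrelated to arm, either constant or varying between men. The share mediated came from linear product-of-coefficients models with a Sobel test. Results with 61 per arm:

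| Intoxicated share | Median share 'mediated' | Sobel test significant |
|---|---|---|
| 10% | 5–20% | 2–29% of runs |
| 30% | 19–53% | 23–69% |
| 50% | 33–72% | 40–84% |

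The lower figures come from shares that vary between men and from higher means. At a control mean of 3.5 and a 30% share, for example, the median was 45% with a constant share and 26% with a varying one.

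With no intervention effect (control mean 3.5), the item still predicted the outcome in 84–100% of runs. The arm-to-item path was significant in only 4–5% and the Sobel test in 1–4%, so no false mediated effect arises.

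**The case against.** Several objections have force.

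*A reader might infer that the analysis is bound to show intoxication explaining the effect.* The documents do not support that. The artefact needs a real intervention effect, and at an intoxicated share near 10% a formal test would often be non-significant in this pilot. The protocol gives no figure for the share.

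*A reader might infer that as much as 75% of the effect could be explained away at a mean of 6.* That requires p = 0.5 and phi = 3, and so an SD of √18 = 4.24, well above the 2.7 that the sample size implies. Shares of that order need a lower mean or more overdispersion. If the planning SD was already adjusted for baseline, the raw SD would be larger, but the protocol does not say so.

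*A reader might infer that the item is a strict subset of the primary outcome.* The item is not limited to vaginal sex, the questionnaire also covers anal sex and male partners (Sexual partners), and the full instrument is in a supplementary appendix that is not shown. The overlap is near-complete rather than exact. Since at least half of each man's partners must be female (Inclusion criteria), it remains dominant for most participants.

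*The model is not specified.* The protocol calls it a prognostic model, promises no proportion mediated, gives two other mediators as its examples, and refers to a separate analysis plan. The percentages above therefore show scale and do not predict a planned statistic. Change scores or the log link would alter the size. But the protocol itself fixes both the item's content and its place among the mediators, and any model that links this item to the outcome inherits the overlap.

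*The consequence is limited.* This is one item in an exploratory analysis of a pilot, and its stated use is hedged. That is fair, and it limits the weight of the point.

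**Conclusion.** The point holds as a classification error in the mediator set. The item largely counts primary outcome events over the same window, so a general fall in unprotected sex can look like an effect through intoxication. On an assumed mean of 6, an SD of about 2.7 (phi about 1.2) and an intoxicated share of 20% to 50% that is unrelated to arm, the spurious share is about 23% to 55%. It rises with a lower mean or more overdispersion, and falls if the share varies between men or is near 10%. The mean and the intoxicated share are assumptions, and the SD is inferred. The primary treatment comparison, the sample size and the feasibility aims are not affected. The item should be reclassified before the mediation analysis is run.

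**What to change.** Move the intoxication item in Table 1 from the mediators to the secondary behavioural outcomes, and state under Mediation analyses that the count is not entered in any model that explains total unprotected episodes. Compare it between arms like the other behavioural outcomes.

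If the share of unprotected episodes that occurred when intoxicated is reported, keep it descriptive. It is undefined for men with no unprotected episodes, so a comparison between arms would be made in a group selected after randomisation. Its numerator and denominator may also cover different acts.

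The change needs no new data, no larger sample and no extra burden on participants. The downside is one fewer listed mediator, and intoxication as a mechanism is left untested. Testing it would need a measure independent of condom use, such as occasions of sex while intoxicated with or without a condom, which would mean a new question.
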